## Abbreviations

|         |                                                                            |
|---------|----------------------------------------------------------------------------|
| ACT     | Artemisinin-based Combination Therapy                                      |
| COSTECH | Tanzania Commission for Science and Technology                             |
| CRERC   | Kilimanjaro Christian Medical College Research and Ethics Review Committee |
| DDT     | Dichloro-diphenyl-trichloroethane                                          |
| DMO     | District Medical Officer                                                   |
| DSS     | Demographic Surveillance System                                            |
| EC      | Ethics Committee                                                           |
| EIR     | Entomological Inoculation Rate                                             |
| ELISA   | Enzyme-Linked Immuno Sorbent Assay                                         |
| FGD     | Focus Group Discussion                                                     |
| GPS     | Global Positioning System                                                  |
| Hb      | Haemoglobin                                                                |
| HH      | House Hold                                                                 |
| HRCD    | Health Research Challenge for Delivery                                     |
| ICT     | Immuno-chromatic Test                                                      |
| IRS     | Indoor Residual Spraying                                                   |
| IVCC    | Innovative Vector Control Consortium                                       |
| JMP     | Joint Malaria Programme                                                    |
| KCMC    | Kilimanjaro Christian Medical College                                      |
| LLIN    | Long-Lasting Insecticidal Net                                              |
| LSHTM   | London School of Hygiene and Tropical Medicine                             |
| LT      | Light Traps                                                                |
| MCDC    | Malaria Capacity Development Consortium                                    |
| MRCC    | Medical Research Coordinating Committee                                    |
| MoH     | Ministry of Health and Social Welfare                                      |
| NGO     | Non-Governmental Organisation                                              |
| NIMR    | National Institute for Medical Research                                    |
| NMCP    | National Malaria Control Programme                                         |
| PAMVERC | Pan-African Malaria Vector Research Consortium                             |
| PCR     | Polymerase Chain Reaction                                                  |
| PHC     | Primary Health Care                                                        |
| PI      | Principal Investigator                                                     |
| PMI     | President's Malaria Initiative                                             |
| PMP     | Performance Monitoring Plan                                                |
| PMR     | Performance Monitoring Report                                              |
| PRISM   | Pyrethroid and Repellent Insecticide-treated Sheets against Malaria        |
| RDTs    | Rapid Diagnostic Tests                                                     |
| RFA     | Request for Application                                                    |
| SOP     | Standard Operating Procedure                                               |
| TPRI    | Tropical Pesticides Research Institute                                     |
| TSC     | Trial Steering Committee                                                   |
| UCC     | Universal Coverage Campaign                                                |
| URC     | University Research Co., LLC                                               |
| USAID   | United States Agency for International Development                         |
| WHOPES  | World Health Organisation Pesticide Evaluation Scheme                      |

## EXECUTIVE SUMMARY

The proposed project addresses a critical research question (objective 2 of USAID/URC Request for Application) concerning the operational use of Long Lasting Insecticidal Nets (LLINs) and Indoor Residual Spraying (IRS), namely: Can LLINs sustain transmission reduction gains made by IRS following withdrawal of IRS?

The alliance between LSHTM (UK), NIMR (Tanzania) and KCMC (Tanzania) brings scientists with expertise in vector control research unmatched in Tanzania, encompassing mosquito vector behaviour and ecology, epidemiology, LLIN and IRS coverage and usage, and community-based field trials.

Muleba is an area that was holoendemic for *Plasmodium falciparum* malaria before PMI IRS intervention in 2007. PMI has been conducting IRS in Muleba for the past three years with a single pyrethroid spray round annually. This IRS intervention has already reduced malaria prevalence significantly. Therefore, the setting in Muleba is ideal for research question objective 2. We aim to evaluate the scaling-up LLIN coverage across the whole of the study area and withdrawing IRS in one study arm whilst maintaining a single IRS round in the other arm. The study will run for two years.

The trial design will involve randomised selection of stratified clusters for 2 study arms. The primary outcome measure will be prevalence of parasitaemia and anaemia in children aged 0.5-10 years, measured in cross sectional surveys. Secondary outcomes will include malaria transmission as measured by entomological inoculation rates (EIR) of the mosquito vector species and serological prevalence of malaria, as well as user acceptability of LLINs compared with IRS. It is hoped that a measure of incidence can be introduced, based on clinical malaria diagnosed using RDTs in the health facilities of the district.

The study location and the proposed trial design will provide PMI and National Malaria Control Programme with valuable answers to the key objectives. Findings from this study are expected to inform decision making so that resource utilization can be optimised.

## TECHNICAL APPLICATION

### 1. Background

In Tanzania the 2010 program of the National Malaria Control Programme (NMCP), in collaboration with several international donors (including President Malaria Initiative), will scale up LLIN distribution under the Universal Coverage Campaign (UCC) and spray IRS insecticides in selected regions with the highest malaria prevalence (USAID, 2009). The universal coverage campaign is scheduled to take place in Muleba district at the end of March 2011. Historically control programs have focussed either on IRS or ITN/LLINs. This trend is changing with ambitions towards elimination and we are to see implementation of both IRS and LLIN in several African countries under PMI. One potential control strategy involves using IRS in areas of high transmission to first reduce transmission to a low level before using LLINs to maintain the low

parasite rates while withdrawing IRS. It is essential to conduct cluster randomised trials to determine whether LLINs at high coverage can provide a non inferior replacement of IRS after several cycles of the latter.

The results of the proposed trial will help inform PMI, the Tanzanian NMCP and other African Departments of Health of the potential benefits and detrimental effects of maintaining or introducing IRS alongside scaling up of LLIN distribution. The results will be beneficial to the study communities and similar populations in Tanzania and elsewhere. The study will also provide evidence regarding the cost and effectiveness of 1 round of IRS per year in comparison to scaling up LLINs.

The National Institute for Medical Research (NIMR) and Kilimanjaro Christian Medical Centre (KCMC) are major malaria research organisations in Tanzania. They have a long history of working with the London School of Hygiene & Tropical Medicine (LSHTM) on malaria research under the umbrella of the Pan African Malaria Vector Control Research Consortium (PAMVERC). More recently LSHTM, NIMR and KCMC have evaluated different types of LLIN on behalf of the WHO Pesticide Evaluation Scheme (WHOPES) and the manufacturing industry. They also constitute the field evaluation wing of the Innovative Vector Control Consortium (IVCC) whose purpose is to work with industry to develop new vector control tools such as combination nets and long lasting IRS formulations. Thus the three partners; LSHTM, NIMR and KCMC, are pre-eminent in the development, implementation and evaluation of IRS and LLINs, and with their long history of collaboration form the ideal technical and managerial alliance to conduct the research planned for PMI and advise on future practice.

## **2. Research Plan**

### **2.1. Objectives**

The aim of this research is to determine whether it is necessary to maintain IRS once malaria transmission has been reduced or whether following the scaling-up of LLINs the IRS can be withdrawn and low transmission rates can be maintained equally well with LLINs alone. It will specifically address objective 2 of the RFA:

“Objective 2. In areas where one or more rounds of IRS have been carried out and malaria transmission has been reduced, can LLINs be used to sustain the transmission reduction gains made by IRS following the withdrawal of IRS?”

### **2.2. Basic Study Design:**

The study objective will be addressed as a two-arm cluster-randomised intervention trial.

Study arms:

Study arm A. Yr. 1: One round per annum of high coverage IRS and high coverage LLIN,  
Yr. 2: One round per annum of high coverage IRS and high coverage LLIN.  
Study arm B. Yr. 1: One round per annum of high coverage IRS and high coverage LLIN,  
Yr. 2 – No IRS and high coverage LLIN.

The null hypothesis would be that the intervention arm in which IRS was withdrawn (Study arm B) is inferior to the reference arm in which IRS is retained (Study arm A). The alternative hypothesis is that the LLIN only arm (Study arm B) is non-inferior to the LLIN plus IRS study arm (A), as demonstrated by a difference in prevalence of infection in the two study arms to be no more than a pre-specified margin. If IRS is eventually withdrawn programmatically from areas currently given IRS and LLIN universal coverage, this study would provide assurance that it would be safe to do so without endangering a return to higher transmission levels.

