## 2.4. Hypothesis

This trial will address the following question: In a situation where IRS is thought to have been successfully deployed to reduce malaria transmission, can high coverage LLINs be implemented as a non-inferior alternative to continued IRS plus high coverage LLINs and achieve the same level of malaria control. In terms of study design the trial will, after a baseline year of IRS and high coverage of LLIN in both arms, compare high LLIN coverage along with continued use of IRS in one arm to high LLIN coverage alone in the other.

In year one (baseline) the two study arms both receive one round of high coverage IRS in January-February 2011 and Universal Coverage of LLIN at the end of March 2011. Coverage of both will be assessed. In year two (intervention year) the reference (control) study arm A continues with one round of high coverage IRS in September 2011 and high coverage of LLIN (from the distribution in March), whilst in the intervention arm (B) there will be continued high coverage of LLINs and IRS is withdrawn. The intervention arm should be no less effective than the reference arm.

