#### Objectives of the post-intervention surveys

*Compare the two study arms in terms of:*

1. Malaria prevalence
2. Mean haemoglobin (g/dL) in children under 5 years old
3. Sero-conversion rates

4. Entomological Inoculation Rate (EIR) for each mosquito vector species.
5. Relative population density for each mosquito vector species

*Evaluate:*

6. Usage and perception of LLIN in an environment of reduced IRS.
7. Coverage and perception of IRS and the withdrawal of IRS
8. To determine the effect of LLIN integrity on malaria prevalence

Household Survey – modifications from the pilot

The survey will include additional information on, educational status and occupation, social economic status (SES) and house structure. Additional question on nets will be elaborate to evaluate the LLIN distribution campaign process of March 2011, source of net and net usage and reason of non usage. The IRS section will also include in-depth information on coverage and perception and acceptance of IRS.

It is planned to use a Personal Digital Assistant (PDA) for the household questionnaire during baseline and post interventions cross sectional surveys.

Parasitological Survey– modifications from the pilot

Additional data and test will be performed:

- History of fever in the last 48 hours will be recorded
- Only individuals with current or history of fever in the last 48 hours will be tested for malaria with an RDT.
- **PCR.** A blood spot on filter paper will be collected for PCR determination of sub-patent infections since prevalence is low. This is to be done for all individuals. The presence of parasite may have been much reduced as a result of the previous IRS campaigns.
- **Force of infection as determined using serology:** A blood spot on filter paper will be collected for serological estimation of antibodies to malaria. Which individuals will be sampled for serology will be determined by the pilot and through discussion with serology specialists. As vector control has been ongoing since 2007 serology will show us the change in the force of infection over time since IRS intervention began. The purpose is to determine whether malaria prevalence fell around the time IRS spraying began.

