#### Insecticide resistance in vector and nuisance-biting mosquitoes

Pyrethroid resistance is a particular concern in areas of high selection pressure where pyrethroid IRS and pyrethroid LLINs are used. WHO resistance tests will be carried out once a year using pyrethroid test papers in WHO kits. Percentage mortality, median time to knockdown, and LD50s response to pyrethroids will be measured. Longitudinal sampling of mosquitoes and testing for kdr and other resistance markers will allow detection of resistance and selection in the two study arms.

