|                                                                                                                     | Detection of Pf infection by RDTs, bloodslides, PCR | 
 
3000 children surveyed
 
3000 RDTs taken and read
 
3000 slides stained and double read
 
PCR detection of Pf from bloodspots
 
Pf % prevalence by age group and diagnostic technique
 
                                                                                                                                                                                                                                                                    | Feb-March 2012
“
End April 2012
“
“ |
|                                                                                                                     | Sero-prevalence (bloodspot ELISA)                          | 
 
Impact of IRS on sero-conversion rates by age group and spray history
 
                                                                                                                                                                                                                                                                                                                                                                                                                              | May 2012                                        |
| Cross-sectional post intervention survey
B
(100 children from ~100households in each of ~30 clusters)  | Questionnaires                                             | 
 
Completion of questionnaire survey in ~7100houses within each of 30 clusters
 
Household census & risk factors data 
 
Socioeconomic data
 
Bednet usage; IRS and other insecticide use
 
 
 
% of children who slept under an ITN/LLIN on the previous night
 
% of households with evidence of IRS in
 
                                                                                                                | April-May 2012                                  |

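### The decision rule compares arm B with arm A only, so it can show that withdrawing IRS is no worse than keeping it, but not that the gains were sustained, as Objective 2 and the promised assurance require

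*Protocol*

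**What the plan says.** Section 2.1 takes its objective from the funder's request: "can LLINs be used to sustain the transmission reduction gains made by IRS following the withdrawal of IRS". The aim just before it mixes level and comparison, asking whether "low transmission rates can be maintained equally well with LLINs alone". Section 2.2 then states what a positive result would mean for programmes: "this study would provide assurance that it would be safe to do so without endangering a return to higher transmission levels".

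The rule that leads to that conclusion is purely between arms. Section 2.2 defines non-inferiority "as demonstrated by a difference in prevalence of infection in the two study arms to be no more than a pre-specified margin". Section 2.4 restates it: "The intervention arm should be no less effective than the reference arm". Section 2.5 gives effect estimates relative to the reference arm, Section 2.6 sizes the trial on the between-arm margin, and the post-intervention survey objectives in Section 3.3.3 open with "Compare the two study arms in terms of".

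For malaria prevalence, the June 2011 baseline survey has two stated uses in the arm comparison: checking that the arms are similar (Section 3.3.3) and adjusting for imbalance (Section 3.8). No criterion sets arm B, or either arm, against its own pre-withdrawal level.

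**The concern.** Sustaining a gain, and not returning to higher transmission, are statements about level over time. A small difference between concurrent arms fits two very different situations: both arms stayed low, or both rose together.

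The protocol itself names a mechanism that could act on both arms. Section 3.5.3 says: "Pyrethroid resistance is a particular concern in areas of high selection pressure where pyrethroid IRS and pyrethroid LLINs are used". The executive summary describes the IRS as pyrethroid. Resistance could therefore weaken sprayed walls and nets together and make the arms look alike.

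A non-inferior result would then be read, in the words of Section 2.2, as assurance about withdrawal, although infection had gone back up. The result is meant to inform programme decisions, so the wording of the conclusion matters.

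**Working it through.** **Inputs.** 15 clusters per arm (Section 2.3); m = 100 children per cluster, 80% power, 5% significance, between-cluster coefficient of variation k of 0.1 to 0.3 with one scenario of 0.6 (Section 2.6 and Table 1). Section 2.6 says cost requires a relative margin of 50% or more and treats 5 points as the largest meaningful absolute difference. Section 2.8 reports pre-IRS prevalence of 10–31% and a two-fold fall to an average of 9.8%, so a doubling from 10% to 20% would undo the reported gain.

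**Step 1: reproduce Table 1.** For non-inferiority, with equal true prevalence p and margin d:

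c = 1 + (z₀.₉₅ + z₀.₈₀)² × [2p(1−p)/m + 2k²p²] / d²

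Last row (p = 0.04, d = 0.03, k = 0.6): 1 + 6.18 × (0.000768 + 0.001152)/0.0009 = 14.19, rounded up to 15, as printed. All 14 non-inferiority entries match with one-sided 5%. All 14 superiority entries match the corresponding formula with two-sided 5%. The sample size is not in question.

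**Step 2: chance of declaring non-inferiority when both arms truly stand at p.**

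SE = √{[2p(1−p)/m + 2k²p²]/15}; probability = Φ(d/SE − 1.645)

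At p = 0.20, k = 0.3: SE = √[(0.0032 + 0.0072)/15] = 0.0263.
- 5-point margin: Φ(0.05/0.0263 − 1.645) = Φ(0.25) = 60%.
- 50% relative margin (10 points): Φ(0.10/0.0263 − 1.645) = Φ(2.15) = 98%.

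| True prevalence, both arms | k | 5-point margin | 50% relative margin |
|---|---|---|---|
| 10% (no rise) | 0.3 | 94% | 94% |
| 20% | 0.3 | 60% | 98% |
| 20% | 0.2 | 78% | 99.9% |
| 20% | 0.1 | 92% | over 99.9% |
| 30% | 0.3 | 39% | 99% |

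In Table 1's only 15-cluster non-inferiority scenario (4%, 3 points, k = 0.6), a doubling to 8% in both arms gives 44% with the 3-point margin and 91% with the 75% relative margin.

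**Step 3: can the planned data show the change within arm B?** Take a rise from 8% to 16%, k = 0.3, 15 clusters, 95% confidence.
- Surveys treated as independent: variance per cluster = 0.000736 + 0.001344 + 0.09 × (0.0064 + 0.0256) = 0.00496; SE = √(0.00496/15) = 1.82 points; × 2.048 (t, 28 df) = ±3.7 points.
- Clusters keeping their relative rank, each rising in proportion: variance = 0.000736 + 0.001344 + (0.3 × 0.08)² = 0.002656; SE = 1.33 points; × 2.145 (t, 14 df) = ±2.9 points.

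An 8-point rise would be plain. If prevalence stayed at 10%, the power to rule out a 5-point rise would be 94% (independent) to 99.8% (between-cluster variation cancels) at k = 0.3.

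**Step 4: dates.** The baseline survey is in June 2011 (Section 3.3.1) or June–July (Section 4 text). Survey B is in June 2012 (Section 3.3.1) or June–July (Section 4 text). The Section 4 table instead gives "April-May 2012" for the Survey B questionnaires and May–June 2012 for parasitology. A same-season comparison needs one agreed window.

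**The case against.** The strongest reply is that the randomised, concurrent comparison is the right causal test. If both arms rise equally, withdrawal did not cause the rise. Parts of the text, such as the aim in Section 2.1 and the question in Section 2.4, are openly comparative. This stands, and it is why the primary test should not change. It does not make the comparison an answer to whether gains were sustained.

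A reader might infer that nothing in the plan would reveal a shared failure. The protocol does not support that. It plans cone bioassays of sprayed walls, checks of net efficacy, yearly resistance tests, testing for resistance markers, serology for force of infection over time, and mosquito counts. These would help to explain a joint rise, but none is tied to the conclusion.

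A reader might also infer that no before-after analysis will be done. Section 3.8 leaves the full analytical plan for later, so one may exist. The hypothesis and the promised conclusion, however, are fixed in this protocol.

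A further reply is that a before-after contrast is weak evidence. June 2011 is about 4 months after spraying in all clusters. June 2012 is 8 months after the September 2011 round in arm A. Rainfall differs between years. This too stands, and it argues against making the within-arm change a co-primary gate.

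**Conclusion.** The point holds as a mismatch between the question and promised assurance on one side and the decision rule on the other. It is not an error in the sample size or in the choice of primary test.

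Its size depends on the margin, which Section 2.6 does not settle as absolute or relative. At 20% in both arms and k = 0.3, non-inferiority is declared about 60% of the time with 5 points and about 98% with a 50% relative margin. The lower figure is closer to the 5-point cap and to the section's own warning about large relative margins at high prevalence. With a relative margin, the shared rise makes the declaration more likely than no rise does (98% against 94%).

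These figures assume equal true prevalence in both arms, an assumed size of rise, k unchanged as prevalence rises, and one-sided 5%, which is what reproduces Table 1. It would go too far to infer that a shared rise always yields a non-inferior result. Take 16% in both arms, k = 0.3 and an observed difference of zero. The SE is 2.2 points and the upper limit is 3.6 points (one-sided 95%) or 4.3 points (97.5%). Both lie inside 5 points, but the second exceeds the 4 points that Table 1 uses as the wider margin at 8%.

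**What to change.** 1. Keep arm B against arm A as the sole primary test.
2. Limit the Section 2.2 conclusion to what that test shows: nets alone are no worse, within the margin, than continued IRS plus nets.
3. Pre-specify a supporting cluster-level estimate, with confidence interval, of the change in prevalence from June 2011 to June 2012 in arm B, with arm A's change beside it. Use the same diagnostic method and age range in both surveys. Use the June 2011 baseline and not the pilot, because clusters are chosen for high pilot prevalence and would be expected to regress towards the mean.
4. Claim that gains were sustained only if this supporting analysis agrees. Otherwise report non-inferiority, with gains not shown to be sustained.
5. Reconcile the Survey B dates between Section 3.3.1, the Section 4 text and the Section 4 table, so that the season matches the baseline survey.

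The cost is revised wording and one extra analysis of surveys already planned, with no added clusters or children. The downside is that the before-after estimate is not randomised and carries differences in rainfall and time since spraying. It should be reported with that caution, as a qualifier of the primary verdict.
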